# 4. STUDY POPULATION

## 4.1 Population (base)

Otherwise healthy patients (men and women) ≥18 years of age with genetically proven Birt-Hogg-Dubé syndrome and facial fibrofolliculomas.

Patients with Birt-Hogg-Dubé syndrome ascertained in the Netherlands by the European Birt Hogg Dubé consortium. We are aware of 40 families with a total of 100 patients and we are in the process of ascertaining more. Recruitment of the required number of patients (20, see below) should present no problems.

## 4.2 Inclusion criteria

Minimum age of 18 years, facial fibrofolliculomas with at least 10 lesions, entered in a screening program and free of malignancy as determined during screening (already had a baseline MRI or CT-scan in the last 12 months). Otherwise healthy. Able to understand instructions. Fibrofolliculoma diagnosis must be histologically confirmed. Mutation status must be known. For females: not pregnant and willing to use both oral and barrier contraceptives during the treatment period.

## 4.3 Exclusion criteria

Proven or suspected malignancy of skin or other organs. No histological confirmation. Skin lesions other than fibrofolliculomas that might worsen under rapamycin such as active infections. Pregnancy or failure to comply with contraceptive measures. Not able to comprehend instructions. Age under 18 years. No proven mutation. Less than 10 fibrofolliculomas. Planned facial surgery in the treatment period. Concomitant disease requiring systemic immunosuppressive treatment during the trial period or within 30 days before starting therapy. The use of facial topical immunosuppressive treatment or facial topical drugs that interfere with rapamycin during the trial period or within 30 days before starting therapy. Not capable of informed consent. Drug- or alcohol abuse. Tendency to form keloids.

## 4.4 Sample size calculation

Sample size is calculated to detect a difference of 35% in response as measured with a 7-point scale with a power of 90% and a type 1 error, 2 sided, of 0.05. Using McNemar’s chi-square test for matched pairs (each patient serves as his/her own control) we would need 17 patients. Taking into account 15% drop-outs we need to include 20 patients.

# 5. TREATMENT OF SUBJECTS

## 5.1 Investigational product/treatment

Test treatment:

- Rapamune 1 mg/ml
- Active ingredient: rapamycin
- Strength: 0,1%
- Dosage form: oral solution, in this study for topical use
- Manufacturer: Wyeth Pharmaceuticals

After randomisation, patients apply rapamycin 1 mg/ml oral solution (Wyeth) to one predefined skin area on one facial half, twice daily, during 6 months. The other facial half will be similarly treated with a placebo consisting of the excipients only. One of the excipients is propylene glycol which defines the colour (yellowish) and smell of the solution. Because rapamune and placebo solution both contain this substance, the solutions can not be distinguished. For preparing the placebo solution the excipients (polysorbate 80 and Phosal PG 50) will be merged into a container. Later water is added and everything is mixed for 10 minutes. Regarding storage and transport we may state that rapamycine and placebo both will be stored at a temperature of 2-8°C. Bottles will be packed in firm export material (cardboard) so that bottles can impossibly break.

## 5.2 Use of co-intervention

The use of topical immunosuppressants in the face, including tacrolimus and corticosteroids and the use of any other facial dermatological medication that is interacting rapamycin, is not allowed. Topical medication that is used outside the face can be allowed after consultation with the principal investigator. Oral immunosuppressive medication is not allowed. Any other oral medication is only allowed after consulting the principal investigator.

Females should ensure adequate contraception using oral contraceptives and barrier methods. Local surgical procedures including laser surgery are not allowed. If there is a medical necessity for such procedures the patient must discontinue the trial.

# 6. INVESTIGATIONAL MEDICINAL PRODUCT

## 6.1 Name and description of investigational medicinal product

Rapamune 1 mg/ml oral solution (Wyeth).

## 6.2 Summary of findings from non-clinical studies

In our study we apply this solution topically to treat fibrofolliculomas in BHD.

Topical rapamycin has been used before in several studies. These studies have shown that topical rapamycin was effective in mouse models for different dermatological diseases. A study in nude mice bearing subcutaneous, TSC-related tumours, showed that application of topical rapamycin inhibits TCS tumour growth and improves survival compared to the vehicle cohort. The study also demonstrates that 0,4-0,8% rapamycin applied topically penetrates the skin. [17] Topical rapamycin 0,4%-3,6% was effective in a mouse model for irritant dermatitis and 1% topical rapamycin was effective in mouse model of allergic dermatitis.[18]

## 6.3 Summary of findings from clinical studies

Prior clinical studies showed that topical rapamycin is safe and may be effective in some dermatological diseases.

In a randomized double-blind clinical trial, 8% topical rapamycin was effective for the treatment of psoriasis and there was evidence of skin penetration without measurable rapamycin in blood. [15] An open prospective study of 7 women with chronic erosive oral lichen planus (CEOLP) showed that application of topical rapamycin (1 mg/ml) may be effective in some cases, with negligible absorption into blood and minimal side effects. In this study 4 women had complete remission and 2 had partial remission of lesions. Only 1 woman had rapamycin blood levels that were detectable.[16]

A case report describes how treatment with oral rapamycin in a patient with TSC who underwent renal transplantation, reduced facial angiofibromas dramatically.[12]

Summarized, both clinical and non-clinical studies show that topical rapamycin was both safe and effective. Information about Rapamune 1 mg/ml oral solution may be found in the SPC document: Annex D1, D2 and D3.

## 6.4 Summary of known and potential risks and benefits

A potential risk when participating in this study is an allergy for one of the components of rapamune oral solution. We do not foresee any other risks. Prior research has shown that local application is safe and does not lead to significant plasma levels.

A benefit of topical rapamycin is that side effects are negligible. This contrasts with treatments that are used presently, such as laser and surgical interventions. Complications like scar formation, inflammation, hypo- and hyperpigmentation may occur.

Topical application of rapamycin is potentially associated with temporary irritation and a tingling or slightly painful sensation. However, this is likely due to the alcohol in the excipient. These minor side effects can be easily controlled with a fatty ointment.

Other potential benefits are prevention of new tumour growth and reduction in size and/or number of tumours.

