### 7.1.3. Other study parameters

Other study parameters (baseline characteristics) will be presented in a table.

These other parameters are age, sex, count and average size of FF, previous treatment for FF, age of presentation of FF, other medication used during the trial, medical history.

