## 10.3 Benefits and risks assessment, group relatedness

Participation requires patients to apply rapamycin liquid and placebo liquid twice daily.

Participation in the study will take the patient 5 minutes a day, plus the control visits every 3 months that will take approximately 30 minutes. As described above, a potential risk when participating in this study is an allergy for one of the components of rapamune oral solution.

Furthermore, local irritation due to the excipient, which contains alcohol, is possible but this can be easily controlled. There will be one biopsy for patients who have not yet undergone one. A skin biopsy is taken by means of a 3 mm punch after injection of local anaesthetic which is briefly painful. A properly taken biopsy will leave no or minimal scarring. If a patient has a known tendency to form keloids or hypertrophic scars, a biopsy is undesirable for cosmetic reasons.

Previous studies have shown that topical application of rapamycin is safe and does not lead to therapeutic plasma levels. The benefit for the patients is in the potential reduction in facial tumour size and number. For BHD patients in general the benefit will be an easily used topical treatment with which fibrofolliculomas may be treated or prevented.

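### Allergy to the study solution is a named risk of participation, but the eligibility criteria (4.2, 4.3) do not exclude patients with a known hypersensitivity

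*Protocol*

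**What the plan says.** The protocol names the risk three times: in the summary, in section 6.4 ("A potential risk when participating in this study is an allergy for one of the components of rapamune oral solution") and in section 10.3 ("As described above, a potential risk when participating in this study is an allergy for one of the components of rapamune oral solution"). In 6.4 the next sentence says that no other risk is foreseen, although the section goes on to describe temporary irritation.

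The solution goes on both sides of the face. Section 5.1 states: "The other facial half will be similarly treated with a placebo consisting of the excipients only". It names the components: "For preparing the placebo solution the excipients (polysorbate 80 and Phosal PG 50) will be merged into a container", and "One of the excipients is propylene glycol". The summary and sections 6.4 and 10.3 add that the excipient contains alcohol.

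On eligibility, the nearest wording in 4.2 is "Otherwise healthy. Able to understand instructions". Section 4.3 ends with "Not capable of informed consent. Drug- or alcohol abuse. Tendency to form keloids" and has no item on allergy. Section 7.1.3 lists, among the characteristics to be tabulated at baseline, "age of presentation of FF, other medication used during the trial, medical history". Section 8.2 deals with allergy once treatment has begun: a patient whose local irritation turns out to be allergic leaves the trial.

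**The concern.** The eligibility list is the rule that decides who is enrolled. Here it is silent on the drug risk that the protocol itself puts first. A patient who already knows of an allergy to rapamycin, polysorbate 80, Phosal PG 50 or propylene glycol meets no written bar to entry, and the protocol reacts only after exposure.

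What is at stake is an avoidable reaction on the face in people treated for benign lesions. With an excipient allergy there is no unexposed side, since both bottles contain the excipients and both are applied twice daily for up to 6 months. Section 8.2 records the affected side so that rapamycin and placebo effects can be told apart, but a reaction on both sides would not identify the cause. The first scheduled follow-up is at 3 months, so before then detection depends largely on the patient making contact.

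**Working it through.** No arithmetic applies beyond counting. The check sets the risk statements beside the rules that should act on them.

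1. **Where the risk is named.** Summary, 6.4 and 10.3: 3 places.
2. **Inclusion criteria, 4.2.** Of 6 sentences, 0 concern allergy, hypersensitivity or intolerance. The requirement of general good health is the closest, but a well person with a contact allergy can reasonably be regarded as meeting it.
3. **Exclusion criteria, 4.3.** Of 14 statements, 0 concern allergy. The closest is the item on other skin lesions that rapamycin might aggravate. It covers lesions already present, not sensitisation, and does not mention excipients.
4. **Screening visit, 7.3.** There are 5 items: the eligibility decision, physical examination, a biopsy where needed, the patient information and a pregnancy test. None concerns allergy. The eligibility decision refers back to 4.2 and 4.3, so it adds nothing here.
5. **Baseline data, 7.1.3.** Medical history is collected to describe the sample. Allergy is not named, and no eligibility decision depends on it.
6. **After enrolment, 8.2.** Non-allergic irritation is treated with a temporary corticosteroid and the patient continues; allergic irritation ends participation. Both steps follow exposure.
7. **Comparison within the protocol.** Section 10.3 says that a tendency to form keloids makes a biopsy undesirable, and 4.3 excludes that tendency. The same section names allergy to the solution, and 4.3 has no matching item. So a named biopsy risk was turned into an exclusion, while the named drug risk was not.

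Read together, the risk is stated in 3 places, handled in 1 place after exposure, and handled in 0 places before it.

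**The case against.** The strongest reply is that this is an omission, not an error. The sentence in 6.4 is a correct disclosure, no section contradicts another, and nothing in the protocol suggests that any candidate has a known allergy. That is right, and it is why the point is minor.

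There are also practical safeguards. Candidates come from the databases of the two centres that already follow them, receive a letter from their own doctor and are called by the investigator (10.2). Medical history is collected. The investigator may withdraw a patient for urgent medical reasons (7.4), and adverse events are followed until they resolve or stabilise (8.3). These make it less likely that a known allergy goes unnoticed, but none is an eligibility rule. The general health requirement leaves room for judgement, but does not reliably cover contact allergy.

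Finally, several annexes are not at hand: the trial monitor forms (F4), the product information (D1 to D3) and the patient information (E1). Any of them may contain an allergy question or a contraindication. This limits the screening point to the text of 7.3. It does not change the reading of 4.2 and 4.3, which do not refer to those annexes for this purpose.

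**Conclusion.** The concern holds. The exclusion list is incomplete: hypersensitivity to the study solution is a named risk, and a patient known to have it is not excluded by the written criteria. The finding on 4.2 and 4.3 is firm; the finding on screening rests on the text of 7.3 alone.

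No numerical size can be given, because the number of candidates with a known allergy is not stated. An exclusion would remove only known cases. First-time reactions would still occur and would still be handled under 8.2. Nothing here affects the sample size, the power or the primary comparison. It is a small safety improvement, worth making because it is specific and nearly free.

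**What to change.** Add one exclusion to 4.3: *known hypersensitivity to rapamycin or to any excipient of the study solution or placebo*. Add a matching history question to the screening visit in 7.3. The question can list the components that the protocol already names: polysorbate 80, Phosal PG 50, propylene glycol and alcohol. If Annex F4 already contains such a question, only the line in 4.3 and a cross-reference are needed.

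The cost is one line, one question and possibly a very small number of ineligible candidates. Section 4.1 counts about 100 known patients for 20 places and foresees no difficulty in recruiting. The sample size and the analysis stay as they are.

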## 6.5 Description and justification of route of administration and dosage

The skin tumours are benign. Although cosmetically disturbing and sometimes even disfiguring, we do feel that oral administration of rapamycin cannot be justified because

this mode of administration has potentially severe side effects. A further description of rapamycin solution is given in chapter 5.

## 6.6 Dosages, dosage modifications and method of administration

Patients apply rapamune 1 mg/ml oral solution (Wyeth) to one predefined skin area on one facial half, twice daily. Patients will be instructed in the procedure to avoid dosage artefacts.

The other facial half will be similarly treated with a placebo consisting of the excipient only. Study medication will be provided in bottles fitted with a syringe adapter. A dosing syringe should be used to withdraw the right amount of solution from the bottle. The patient will be instructed how to use the syringe and to wash hands after each application.

For patient instructions see Annex E4.

Sides to be treated will be randomized once, medication will be labelled with study number, patient initials, visit number, date of distribution and facial side to be treated where LEFT and RIGHT are taken to be determined from the patient’s POV.

## 6.7 Preparation and labelling of Investigational Medicinal Product

Prior to start of the study, rapamycin oral solution will be provided by Wyeth pharmaceuticals. ACE Pharmaceuticals in Zeewolde will be responsible for packaging and labelling the study medication. They will also produce the placebo solution. Rapamune and placebo solution will be packaged in amber glass 20 ml bottles. Decanting of rapamune will take place at a temperature of 2-8 °C at nitrogen conditions to preserve solution quality.

As described above the study medication will be delivered in 20 ml bottles, 6 for each facial half, fitted with a syringe adapter. With a dosing syringe patients withdraw 0,25 ml solution twice daily. . Coding of bottles will be according to the randomisation list.

The following information shall appear on the labels:

ALLEEN VOOR GEBRUIK BIJ KLINISCHE STUDIE

**RECHTS** of **LINKS**

Vloeistof, voor uitwendig gebruik.

2x daags aanbrengen op het gezicht.

Zie patiënten informatie voor meer gegevens.

Studienummer: xxxxx

Houdbaarheid na openen: 1 maand

Bewaren in de koelkast (2-8˚C)

Buiten het bereik en zicht van kinderen bewaren.

Because of a 30 day shelf life of an opened bottle, decanting of rapamune - that requires opening bottles – will be done in 6 stages, ones every month. After preparation at ACE Pharmaceuticals the study medication will be sent directly to the patient by post, so treatment can start immediately. In this way we can guarantee a good quality of rapamune, as patients will be out of solution in exactly one month.

## 6.8 Drug accountability

Subjects should return all used and unused medication / bottles to the investigator. Medication will be collected and returned to the pharmacy.

# *7.* METHODS

## 7.1 Study parameters/endpoints

### 7.1.1 Main study parameter/endpoint

The main study parameter is the change in lesion size and count (severity) as measured by the investigator, the patient and two independent dermatologists. For lesion size we use the average size of fibrofolliculomas in millimetres.

Severity is indicated on a 7-point scale:

-3= strong worsening

-2= moderate worsening

-1= minimal worsening

0= no improvement

1= minimal improvement

2= moderate improvement

3= strong improvement

Significant regression is defined as a difference in assessment by at least 2 of 3 observers, with at least +2 points. The observers are the investigator and two independent physicians. Assessment of size and count is made on the basis of medical photos of the face. These photos will be standardized; same distance, background, colour and light profile etc.

Confirmation by visual examination.

Professor [name], professor in clinical epidemiology of Maastricht UMC has advised us to use this 7-point scale. Given the fact that there are no previous randomized controlled trials in the BHD syndrome, there is no previously validated scale that we can use for this disease. That is why we have chosen for a 7-point Likert scale. It is known that the Likert scale has good measurement properties and it is used often in trials in which skin changes have to be assessed [19, 20].

During the study we will determine the intra- and inter-observer variability by means of a weighted kappa test. Per patient 2 photographs will be assessed with the 7-point scale; at 3 months and at 6 months. These photographs will be compared with a baseline photo. To measure the inter- and intra observer variability we need at least 3 observers. These observers will be the researcher and two independent physicians. They will assess every photo twice. To prevent bias, the assessments must be at least 2 months apart. Besides evaluation based on photographs, the researcher as well as the patient can assess facial progress during the appointments. These assessments are not included in the analysis, only the results based on the photographs provided by the researcher, physician 1 and physician 2 will be used. This means there will be 6 scores for every patient per follow-up visit. Of these results, the most frequently given score will be used for the analysis.

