# 3. STUDY DESIGN

The study is double-blind placebo-controlled randomized with the patient him/herself as an internal control. To get enough power we aim to include 20 (see power analysis) adults ≥18 years with Birt-Hogg-Dubé syndrome. Inclusion will take place in two hospitals in the Netherlands; Maastricht University Medical Centre and VU Medical Centre Amsterdam. After inclusion patients are treated with rapamycin in one facial half and a placebo in the other. Patient and physician are blinded until the end of the study. The solution (placebo and verum) is applied according to standardized instructions. The study will proceed according to standardized trial monitor forms (Annex F4). These forms describe how the patient is to be examined at each visit. The skin will be evaluated by 3 observers; the investigator and two dermatologists. They will assess a difference in fibrofolliculoma status on a 7-point rating scale ranging from -3 (strong worsening) to +3 (strong improvement). Although patients evaluate their skin on this scale too, we will not include their measurements in the analysis because of bias. For further explanation see chapter 7.

Patients will be followed-up at 3 months and at 6 months.

It is likely that, during the study, one facial half will improve because of treatment with rapamycin. However, we do not think it is ethical to ask our patients to deal with one improved facial half and one unimproved facial half. Moreover, when patients see a difference between facial sides, they might apply the solution, that they think is the effective one, on both facial sides. To prevent this situation we developed the following study design:

When a clear difference arises between facial sides, blinding will be broken and we will proceed with an open-label study. There are a few conditions to break the blinding, pointed out below.

- Two of three observers have to see a significant difference. This means that there must be an improvement (or worsening, which we don’t expect) of at least 2 points on the 7 point rating scale.
- When there is a significant difference, the blinding will be broken. Then it will also become clear whether the improved side is the rapamycin-treated side. In this case patients are allowed to use rapamycin on the entire face.
- When patients see a difference between the left and right facial side themselves, they can make an earlier appointment.

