## 7.3 Study procedures

Conduct of the study

The first visit (screening) includes:
- In- or exclusion, in case of inclusion:

- Physical examination according to protocol, especially lesion size and count
- Biopsy of a representative tumour (if not yet undergone one)

- The patient already has the patient information; this has been sent before the first visit.

- For women: pregnancy test

The second visit (baseline) includes:

- Physical examination according to protocol

- Standardized medical photography of the face. (All photos will be assessed by the investigator and two independent physicians).
- Instruction of patient (see Annex E4), provide study medication according to randomization

Follow-up visits will take place at 3 months and at 6 months. At each follow-up visit, unused study medication will be taken back and new medication is dispensed. Unused medication is weighed to ensure protocol compliance.

At the first follow-up visit at 3 months it will be assessed if unblinding is needed.

Physical examination and medical photography are part of regular care/medical treatment.

Treatment with rapamycin solution (and placebo solution) and pregnancy tests are part of the study.

See also trial flow-chart: Annex F4.

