## 8.2 Adverse and serious adverse events

Adverse events are defined as any undesirable experience occurring to a subject during a clinical trial, whether or not considered related to the investigational drug. All adverse events reported spontaneously by the subject or observed by the investiga­tor or his staff will be recorded.

When there is a possible adverse event, the trial physician will consult the PI who will then take appropriate action based on his assessment. An example of an adverse event related to the investigational drug (an adverse reaction) is local irritation after application of rapamycin. If this is not allergic, the trial will continue and the patient will get a corticosteroid temporarily. When local irritation is based on an allergic reaction the patient will be excluded.

When a local side effect appears, the affected side of the face will be recorded on the study forms so that it is possible to check afterwards whether the adverse event was caused by rapamycin or the placebo.

A serious adverse event is any untoward medical occurrence or effect that at any dose results in death;

- is life threatening (at the time of the event);
- requires hospitalisation or prolongation of existing inpatients’ hospitalisation;
- results in persistent or significant disability or incapacity;
- is a congenital anomaly or birth defect;
- is a new event of the trial likely to affect the safety of the subjects, such as an unexpected outcome of an adverse reaction, lack of efficacy of an IMP used for the treatment of a life threatening disease, major safety finding from a newly completed animal study, etc.

All SAEs will be reported to the accredited METC that approved the protocol, according to the requirements of that METC.

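### The photograph reading in Section 7.1.1 yields one score per face per reading, but the McNemar comparison in Section 9.2 needs a separate response for each facial half, and one of the three readers also has visit knowledge

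*Protocol*

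**What the plan says.** Protocol Section 7.1.1 bases the main parameter on photographs: "Assessment of size and count is made on the basis of medical photos of the face". It adds "Per patient 2 photographs will be assessed with the 7-point scale; at 3 months and at 6 months", each compared with a baseline photograph. The readers are the investigator and two independent physicians, and Section 7.3 repeats this: "All photos will be assessed by the investigator and two independent physicians". Each reads every photograph twice, at least two months apart. The protocol counts six scores per patient at each follow-up visit and carries the most frequent one into the analysis. Significant regression requires at least 2 of 3 observers at +2 or more; Section 7.1.1 words this as a difference in assessment.

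Section 9.2 compares rapamycin with placebo by McNemar's test for paired samples. Section 4.4 sizes the trial on a "difference of 35% in response as measured with a 7-point scale".

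On the patient's own rating, Section 3 says: "Although patients evaluate their skin on this scale too, we will not include their measurements in the analysis because of bias". Section 7.1.1 lets both the researcher and the patient judge progress at appointments, and leaves those judgements out of the analysis. Section 3 lets patients who notice a side difference come earlier, and describes what to do when they see more improvement than the observers. Section 7.3 has the need for unblinding assessed at the 3-month visit.

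**The concern.** McNemar's test works on pairs: did the rapamycin half respond, and did the placebo half respond? The reading in Section 7.1.1 is described per photograph and per patient, not per half. It is therefore not stated how two responses arise from one carried-forward score.

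If readers judge both halves from the same image, they may push them apart (contrast) or pull them together (halo). Either changes the response difference, which is the quantity that the trial is sized on and will report.

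The protocol identifies the patient's opinion as a source of bias and excludes it. Yet a reader who may know that opinion, and in some patients the allocation, contributes 2 of the 6 scores.

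**Working it through.** **1. The plan's own sample size.** Inputs from Section 4.4: a 35-point difference, "with a power of 90% and a type 1 error, 2 sided, of 0.05", and 17 evaluable pairs. Assume that no patient responds on the placebo half only, so that discordant pairs occur with probability 0.35 and all favour rapamycin. The uncorrected McNemar statistic is (b − c)²/(b + c). With c = 0 it equals b, and it exceeds 3.84 from b = 4. Power = P(X ≥ 4), X ~ Binomial(17, 0.35) = 0.897, which reproduces the stated 90%; 17/0.85 = 20. The calculation thus presupposes a response on each half. If 5% or 10% respond on placebo only, with the same 35-point difference, power is 0.63 or 0.50. The result depends on how each half is classified.

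**2. Score count.** Stated: 3 observers × 2 readings = 6 per patient-visit. With each half scored: 3 × 2 × 2 = 12. The stated count leaves room for one score per face per reading. Neither the most-frequent-score rule nor the 2-of-3 rule is defined per half.

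**3. Does joint viewing create false positives?** Take 17 pairs and no drug effect, and assume that the readers call a one-sided difference in 35% of patients. If the favoured half is the rapamycin half by chance alone (50%), the uncorrected test rejects with probability 0.049. Joint viewing by itself leaves the null intact.

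If the panel's final call agreed with the allocation more often than chance, the rate would be 0.07 at 60% agreement, 0.15 at 70% and 0.30 at 80%. These rates concern the final call of the whole panel, not one reader, and no text supports any particular agreement. They show only that the readings must not depend on knowledge of the side.

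**4. What can joint viewing do to the estimate?** Illustrative model, all inputs assumed. Change on a half = mean (1.3 rapamycin, 0.3 placebo) + shared N(0, SD 0.8) + half-specific N(0, SD 0.6). Each of three readers adds N(0, SD 0.6). Scores are rounded and limited to −3 to +3. Response = at least 2 of 3 readers at +2 or more. Joint viewing multiplies the perceived gap between halves by a factor and keeps the midpoint.

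| Gap factor | Response difference, points |
|---|---|
| 1 (halves read separately) | about 29 |
| 1.3 to 1.5 (contrast) | about 36 to 41 |
| 0.7 to 0.5 (halo) | about 21 to 15 |

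With both means at 0.3 (no drug effect), the difference is zero at every factor, and the uncorrected test with 17 pairs rejects with probability 0.011 to 0.043. This agrees with step 3.

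**5. Timing of the investigator's readings.** The code may be broken at or around 3 months (Sections 3 and 7.3). Repeat readings come at least two months after the first (Section 7.1.1), and the 6-month photographs come later still. For a patient whose code is broken at 3 months, the investigator's second reading of the 3-month photograph and both readings of the 6-month photograph could be made with the allocation known. No provision for coding or shuffling the images stands against this.

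**The case against.** The strongest reply is that allocation masking is provided for. Sides are randomised, bottles are identical and coded, the placebo contains the excipients, and patient and physician are blinded (Sections 5.1 and 7.2). Two of three readers are independent physicians, so the investigator alone cannot meet the 2-of-3 rule. Image presentation can be left to a reading manual, and Annex F4 is not shown. All of this stands as a limit on the size of the problem. It does not answer the score count, because the protocol itself fixes six scores and one carried-forward value.

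It can also be said that side-to-side comparison is a deliberate choice, and that a single comparative score could feed a paired test through its sign. But the scale runs from worsening to improvement, and each photograph is compared with baseline. That describes change over time, not left against right.

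Three stronger readings are tempting and are not supported:

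- **That local irritation tells the investigator which half is active.** Section 8.2 does say "An example of an adverse event related to the investigational drug (an adverse reaction) is local irritation after application of rapamycin". But the Summary and Sections 6.4 and 10.3 attribute irritation to alcohol in the excipient, wholly or as the likely cause, and Section 5.1 gives the placebo the same excipients. Knowing the irritated side does not by itself reveal the allocation.
- **That readers are shown uncropped faces after hearing the patient's verdict.** The framing of the photographs and the timing of the investigator's readings relative to visits are not given.
- **That joint viewing inflates the type I error.** Steps 3 and 4 show that it does not while masking holds.

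**Conclusion.** The point holds in a limited form. The stated reading does not deliver separate half-face scores, although the primary test and the sample size both rest on them. In addition, one of three readers is not separated from visit information or from a broken code.

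The first part follows directly from Sections 7.1.1 and 9.2. The second is an exposure that the protocol leaves open, not a demonstrated bias. Contrast or halo could move the response difference in either direction. Bias in favour of rapamycin would need readings informed by the allocation or by a view that predicts it. The size of either effect cannot be derived from the protocol; the figures in steps 3 and 4 show sensitivity only. The change is worth making because it is cheap and supplies the data that the test requires.

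**What to change.** Amend Section 7.1.1:

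- Prepare single-half images from the existing standardised photographs, mirrored so that left and right look alike, with patient, side and visit labels removed.
- Pair each half with its own baseline half, and present the pairs in random order over patients, halves and visits.
- Have each reader score each half separately, twice as now. This gives 12 scores per patient-visit, 6 per half. State the rule that turns each half's 6 scores into one response for McNemar's test.
- Keep the side-to-side judgement for code-breaking on a separate visit form outside the primary analysis.
- Report a sensitivity analysis on the two independent physicians' readings alone, because the investigator may still recognise patients.

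Cost: a short amendment, a few hours of image preparation, and twice as many but shorter readings. With 20 patients, 2 visits and 2 readings, each reader goes from 80 to 160. Lesions typically lie around the nose (Section 1), so the amendment must say how those near the midline are assigned. The change cannot remove what the investigator learns at visits. Nor does it restore a placebo half in patients who go on to use rapamycin on the whole face after the code is broken.
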